### Statistical analyses

Mean/median values, standard deviations and 95% confidence intervals will be reported. Normality of data will be tested using the Shapiro-Wilk test. General linear mixed model analysis will be utilized to study the differences between time (2 pre-tests and 1 or 2 post-tests) in the CP group. Independent t-tests will be used to compare groups (i.e. CP vs. TD) and paired t-tests to compare the two TD testing times (pre-test 1 and 2). Pearson correlation analysis will be performed to check association between dependent variables. The interference of variables such as PA levels or maturity offset will be controlled if they have a strong linear relationship with other dependent variables. Nonparametric tests may be utilized if necessary. Significance level will be set at *P* < 0.05.

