**Methods:**

Twenty-four children and young adults with spastic CP will be recruited to participate in a 9-month research project with a 3-month training intervention, consisting of two to three 90-min sessions per week. In each session, strength training for the lower limbs and trunk muscles, flexibility training for the lower limbs and inclined treadmill gait training will be performed. We will evaluate muscle strength, joint flexibility, neuromuscular and cardiometabolic parameters. A nonconcurrent multiple baseline design with two pre-tests and two post-tests all interspaced by three months is used. In addition to the CP participants, 24 typically developing age and sex-matched participants will perform the two pre-tests (i.e. no intervention) to provide normative data.

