### Study purpose

The present study has three aims: 1) to investigate the effects of the EXECP intervention on the following variables: gait performance (primary outcome), physical activity level, lower limb muscle strength and joint flexibility, gross motor function, cardiometabolic risk factors, neuromuscular parameters for triceps surae muscle, cortical processing of proprioceptive stimuli evoked by passive ankle dorsiflexions, tibialis anterior (TA) cortico-muscular and intramuscular coherence; 2) to evaluate the retention of the adaptations induced by the intervention after three months; 3) to compare CP and typically developing (TD) individuals in all studied variables using group and matched (age/sex) individual data. The EXECP intervention is composed of a three-month individually tailored exercise intervention containing strength training targeting lower limb and trunk muscles, combined with stretching of diagnosed short muscles and gait training. The primary hypothesis is that the EXECP intervention will enhance gait performance by: a) increasing walking distance in the 6 min walking test; b) increasing ankle dorsiflexion during the swing and stance phase of gait; c) increasing maximal walking velocity, joint net moments and ranges of motion in the lower limb joints. The secondary hypothesis are that the EXECP intervention will: d) increase habitual PA; e) increase maximal isometric and concentric torque and rate of force development for the trained muscles; f) not affect cardiometabolic risk factors such as arterial stiffness, insulin resistance, blood lipids and body fat content; g) increase gross motor function measure (GMFM; [19]) score; h) increase lower limb joint flexibility of the trained muscle groups; i) decrease ankle plantarflexors average joint stiffness and increase joint energy (i.e. area under the torque-angle curve) during slow passive stretching; j) decrease antagonist muscle electromyography (EMG) during maximal voluntary isometric and concentric plantarflexion and dorsiflexion; k) not change spinal mechanisms related to hyperreflexia in the Sol muscle (i.e. Hoffmann-reflex (H-reflex), post-activation depression (PAD) ratio, tonic stretch reflex threshold (TSRT)); l) increase amplitude of cortical responses to proprioceptive stimulation, recorded with magnetoencephalography (MEG) in the primary somatosensory cortex; m) increase cortico-muscular coherence between cortical MEG and TA EMG signals; n) increase intramuscular coherence within TA muscle during a submaximal isometric dorsiflexion and during the swing phase of the gait cycle. No changes in any of the studied variables are expected during the 3-months control period, except if the participant is going through the growth spurt. After the 3-month maintenance period, the values of the studied variables are expected to be in between the control and post intervention values (project aim B). All study variables are hypothesized to show differences between the TD and CP groups (project aim C). It is expected that the comprehensive assessment battery of neuromuscular, brain, cardiometabolic and functional parameters will add valuable information about how people with CP adapt to exercise.

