### Study sample and recruitment

Twenty-four individuals aged 9–24 years with spastic-type CP will be recruited predominantly in the city of Jyväskylä, Finland. Hospitals, physiotherapy clinics and CP associations will be contacted in search of suitable participants. Acquiring the whole sample size in Jyväskylä was not possible, so the recruitment of participants was extended to nearby cities. Furthermore, the coronavirus caused a three-month lockdown in spring 2020, which paused the participation of some participants and delayed recruitment. Twenty-four typically developing age and sex-matched controls will also be recruited from local schools and the University of Jyväskylä. The recruitment has been ongoing since May of 2017 and it is expected to end in December of 2020.

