Maximal isometric and concentric knee flexion and extension will be assessed using a custom-build motor driven dynamometer (NMRC, University of Jyväskylä, Finland). Participants will be seated with the knee joint fully extended (0°) or at 75° of flexion and hip joint flexed at 80°. The distal part of the shank will be secured with a velcro strap to a strain gauge (NMRC, University of Jyväskylä, Finland) capable of measuring both tensile and compressive forces. The position of the strain gauge on the lever arm is adjustable and the distance from the axis of rotation will be individually recorded and reproduced for all following measurements. The rotation axis of both dynamometer and knee will be carefully aligned during a submaximal voluntary muscle action, to take into account the system’s compliance. Participants will be securely stabilized by an assembly of straps fastening both shoulders and connected to a waist belt. The knee flexion test starts with a 2 s maximal isometric muscle action at 0°, followed by an isokinetic (15°/s) concentric effort until 75°. An examiner will keep strong downward pressure at the distal part of thigh to prevent hip flexion during the trial. The knee extension test starts with a 2 s maximal isometric muscle action at 75°, followed by an isokinetic (15°/s) concentric effort until 0°. Torque will be obtained by multiplying the moment arm by the force, and joint angle will be monitored by a linear potentiometer. Both signals will be sampled at 1 KHz with the same hardware and software utilized for the ankle torque tests. The highest attained torque in non-overlapping 5° steps among all trials will be used for analysis. For all four strength tests, rate of force development will be calculated as the maximum slope during the 0–200 ms time period in the isometric part. All measurements will be performed on the most affected leg for the CP group, and on the corresponding leg on the matching control participant. Test isokinetic velocity was chosen based on the slowest intervention training velocity (3 s muscle action for the ankle joint with a ROM of ~ 45°), and because slower velocities are easier to be well performed by the CP participants (observed in the pilot experiment). A preparatory activity consisting of ten progressively stronger efforts from 20 to 90% of the maximum voluntary contraction (MVC) will be performed before each test. Visual torque feedback will be provided in real-time and participants will receive strong verbal encouragement during every trial. Three to five trials with 1–2 min of rest for each test will be performed. In addition to the specific torque-angle analysis described, joint angles in which torque is greater than 90% of the peak concentric torque (i.e. optimum angle; [83]) and greater than 50% of the peak concentric torque (i.e. curve width; [84]) will also be calculated.

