Stretch hyperreflexia of Sol and MG will be assessed utilizing the TSRT [88, 89]. The participant will be seated with the knee joint fully extended and the ankle dynamometer previously described will induce stretches (from 20° of plantarflexion to 0°) on triceps surae at four different velocities: 50, 100, 200 and 300°/s. The stretch velocities will be delivered in a pseudo-randomized and balanced order, yielding 10 stretches in each velocity, with an interval of 2.6–2.9 s. EMG data will be used to determine the joint angle in which the stretch reflex onset occurred (i.e. dynamic stretch reflex threshold, DSRT). A regression line based on a first-order linear equation using all DSRT will be calculated on a stretch velocity-joint angle plot. From the equation, the coefficient of determination, slope and intercept with the x-axis will be attained. The TSRT is the angle at which the regression line intersects with the x-axis, larger values indicate a high level of stretch hyperreflexia. TSRT will be calculated separately for each muscle. In addition to the already established TSRT calculation, we propose using the latency of the H-reflex to take into account the time between the stretch reflex onset and the EMG burst onset. A typical H-reflex latency of 35 ms and a stretch velocity of 300°/s can cause a difference of 10.5° between the stretch reflex and EMG onset, provoking a systematic error towards higher velocities. Thus, all variables in the TSRT will be calculated with and without the latency correction, and the differences will be discussed. Participants will be instructed to relax and will be wearing noise blocking headphones. Trials with EMG exceeding 5% of the isometric plantarflexion MVC in the 500 ms preceding the stretch will be discarded. The EMG burst onset will be defined as a 3SD increase in the RMS of a 20 ms moving average for at least 20 ms compared to the pre-stretch state. Visual inspection of false positives due to small brief muscle activations will be performed and automated onset detection algorithms may also be utilized. H-reflex, PAD and TSRT will be assessed on the most affected limb of the CP group and in the same leg of the age/sex matched control.

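### The CP versus TD comparison uses independent t-tests on individually matched participants, so for outcomes that depend on age and sex its standard errors are too wide

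*Protocol article*

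**What the plan says.** Aim 3 under Study purpose is "to compare CP and typically developing (TD) individuals in all studied variables using group and matched (age/sex) individual data". Study sample and recruitment sets the numbers: 24 participants with CP, and "Twenty-four typically developing age and sex-matched controls will also be recruited".

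Two measurement sections show that the matching is person to person and not only a balancing of the groups. Muscle strength tests the most affected leg in CP and has the control tested "on the corresponding leg on the matching control participant". Neural parameters does the same for the reflex measures, "in the same leg of the age/sex matched control". The tested leg of a control can follow a partner only if each control is assigned to a particular participant with CP.

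Statistical analyses names one test for the between-group comparison: "Independent t-tests will be used to compare groups (i.e. CP vs. TD". Pairing appears only within the TD group over time: "paired t-tests to compare the two TD testing times (pre-test 1 and 2". The mixed model is for time within the CP group. The section also allows control for physical activity or maturity offset when either is strongly linearly related to another variable, and nonparametric tests if needed.

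**The concern.** When pairs share age and sex, outcomes driven by growth tend to be high or low together within a pair. That shared part cancels from the mean CP–TD difference, but the independent t-test leaves it in the standard error. The interval is then wider than the design warrants and the P value too large.

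At stake is aim 3. The hypotheses expect CP–TD differences in all studied variables, and only 24 pairs are available to show them. Matching costs recruitment effort, and the named test gives away the precision that this effort could buy.

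**Working it through.** **Inputs from the protocol article.** 24 participants per group (Sample size); significance level 0.05 (Statistical analyses), taken as two-sided; ages 9–24 years (Inclusion criteria).

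**Inputs assumed.** The within-pair correlation ρ is not given, so a range is shown. Equal SDs in the two groups are assumed first and relaxed afterwards. A true difference of 0.6 SD is used to illustrate power.

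**The plan's own figure.** No power or precision is stated for the CP–TD comparison. The 24 per group comes from a pre-post parallel-groups calculation on walking distance. The printed inputs give a change-score SD of √2 × ln 1.06 = 0.0824 and a difference of ln 1.08 = 0.0770. Then n = 2 × (1.96 + 0.84)² × 0.0824² / 0.0770² ≈ 18 per group, or 20 with the noncentral t. Rounding of the printed inputs spans about 15 to 25, so 24 is compatible with the unrounded values and is not questioned. Nothing below depends on how it was derived.

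**Standard errors, in SD units, n = 24.**
- Independent: √(2/n) = √(2/24) = 0.289, with 46 degrees of freedom (t = 2.013). The 95% half-width is 2.013 × 0.289 = 0.581, whatever ρ is.
- Paired: √(2(1−ρ)/n), with 23 degrees of freedom (t = 2.069). At ρ = 0.3 the half-width is 2.069 × 0.2415 = 0.500; at ρ = 0.5 it is 2.069 × 0.2041 = 0.422.
- Ratio of standard errors with equal SDs: 1/√(1−ρ).
- Ratio when one SD is twice the other: √(5/(5−4ρ)), which is √(5/3.8) = 1.15 at ρ = 0.3 and √(5/3) = 1.29 at ρ = 0.5.

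**Type I error and power** come from simulation of 24 pairs with equal SDs, 100,000 replicates.

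| ρ (assumed) | SE ratio, equal SDs | SE ratio, SDs 2:1 | Half-width, independent | Half-width, paired | Type I error, independent | Power at 0.6 SD, independent | Power at 0.6 SD, paired |
|---|---|---|---|---|---|---|---|
| 0 | 1.00 | 1.00 | 0.581 | 0.597 | 5.1% | 53% | 51% |
| 0.1 | 1.05 | 1.04 | 0.581 | 0.567 | 4.1% | 53% | 55% |
| 0.3 | 1.20 | 1.15 | 0.581 | 0.500 | 2.1% | 54% | 66% |
| 0.5 | 1.41 | 1.29 | 0.581 | 0.422 | 0.7% | 54% | 80% |

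**Break-even.** The paired interval becomes the narrower one once ρ exceeds 1 − (2.013/2.069)² ≈ 0.05.

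**The case against.** The strongest reply is that the correlation is unknown and may be low for many outcomes. Study design calls the expected CP sample highly heterogeneous, and the inclusion criteria admit three levels of gross motor function and both unilateral and bilateral disease. That severity is not shared with the TD match and dilutes the correlation. Aim 3 also covers reflex ratios, coactivation, coherence and cortical responses, for which the documents give no reason to expect 0.3 to 0.5. This stands. It confines the point to outcomes that depend on age and sex.

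A second reply is that maturity offset, a sex-specific function of age and height, may be controlled for, which would recover much of what matching offers. It is a partial answer. The provision depends on the strength of an observed relationship, it is not tied to the CP–TD comparison, and a t-test cannot take a covariate.

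Third, aim 3 speaks of both group and matched individual data, and the independent t-test may be meant for the group part only, with a matched analysis left to a fuller document. A reader might infer that the plan discards the pairs everywhere. The article does not say so. What it does fix is the test for the group comparison, and that test does not fit matched data.

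A reader might also infer that only one visit at a time is compared although both groups have two pre-tests. Statistical analyses does not say which visit, or whether their mean, is used, so that charge is not supported.

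Finally, a strict paired t-test drops anyone without a match, a practical risk given the recruitment difficulty and lockdown described under Study sample and recruitment. This stands and shapes the fix.

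**Conclusion.** The point holds in a limited form. The named test ignores individual matching, and for outcomes that rise or fall with age and sex it gives standard errors and intervals that are too wide. The sizes in the table are conditional on the assumed correlation and, for type I error and power, on equal SDs. Only the direction can be argued from the documents: the age range is wide, and the article itself treats maturation as a confounder.

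It would go too far to say that all confidence intervals and P values for aim 3 are wrong. Where an outcome is unrelated to age and sex, the effect is negligible, and below a correlation of about 0.05 pairing gains nothing. Nor does a positive correlation produce excess false positives: the error is conservative and costs precision and power. The intervention effect is estimated by the mixed model within the CP group and is unaffected.

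**What to change.** In Statistical analyses, replace the independent t-test for CP versus TD by a linear mixed model with group as fixed effect and matched pair as random effect. A group comparison adjusted for age and sex is an acceptable alternative. Both keep participants whose match is missing. A paired t-test is acceptable where all pairs are complete.

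This changes analysis wording only and needs no new data. The price is fewer degrees of freedom, 23 instead of 46 for the paired t-test. If the within-pair correlation is in fact zero, that costs about 2 points of power at a 0.6 SD difference (53% to 51%).

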### Gait training

A portable mechanical treadmill with an inclination of 6° or 7.3° (Vida XL, Venlo, Netherlands) will be utilized for training. Participants are instructed to walk at a comfortable speed, avoiding toe walking and trying their best to attain heel strike. A non-motorized treadmill was chosen because belt movement is attained by pushing it with hip extension and ankle plantarflexion, reinforcing a correct pattern of muscle activation. Verbal feedback will be constantly given during the warm-up to improve gait quality, and the participant will be allowed to stop and rest whenever necessary. In addition to 5–10 min of gait training in every session, all participants will receive a treadmill to take home, and are asked to walk a minimum of 10 min per day every day for the duration of the intervention. An exercise diary will be filled by the participants or their guardians to document the weekly walking durations. During the maintenance period, the participants will choose if they want to keep using the treadmill at home and updating their diary or stop and return it.

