### Testing sessions

Participants will attend the NMRC and the Centre for Interdisciplinary Brain Research (CIBR) at the University of Jyväskylä for all testing sessions. Each testing point (pre-test 1 and 2, post-test 1) consist of three testing sessions (S1, S2 and S3) performed 4 h to seven days apart. Exceptionally, post-test 2 is composed only of S1 and a modified S2. Session 1 (S1) consists of the following tests: joint flexibility, electrostimulation (H-reflex and PAD), muscle strength and tonic stretch reflex threshold. Session 2 (S2) consists of the following tests: blood sampling, body composition and height, arterial stiffness, instrumented gait analysis, six minutes walking test. In session 3 (S3) magnetoencephalography measurements are performed. The modified S2 performed in post-test 2 consists only of the gait tests and height measurement. Table 3 describes the timeline of each testing session. The TD group will only perform the pre-tests 1 and 2. A familiarization session will be performed before the pre-test 1 to get the participants acquainted with the tests. Additionally, this session will be utilized to duplicate some tests of S1 and S2 for a repeatability study.

**Table 3 Tab3:** Testing sessions timetable and procedures

Testing session 1 (S1)	Testing session 2 (S2)	Testing session 3 (S3)
08.00 – Flexibility tests (Hip and Knee)^b^;	08.00 – Blood sampling;	08.00 – Participant preparation;
08.15 – H-reflex/PAD protocol for Sol^a^ at rest;	08.10 – Body composition, height and arterial stiffness;	08.45 – Resting-state;
08.40 – Flexibility test (ankle)^b^;	08.30 – Breakfast;	09.05 – Proprioceptive stimulation for TS^a^;
08.50 – Preparatory activity PF^a^/DF^a^;	09.00 – Participant preparation;	09.30 – Preparatory activity DF^a^;
09.00 – MVC (PF^a^/DF^a^);	09.50 – Gait preparatory activity;	09.40 – Isometric DF MVC^a^;
09.20 – TSRT protocol (TS^a^);	09.55 – 6 × 1 min gait test;	09.50 – Cortico-muscular coherence protocol^a^;
09.30 – Preparatory activity KE^a^/KF^a^;	10.10 – Rest;	10.01 – Session ends.
09.40 – MVC (KE^a^/KF^a^)	10.25 – 6 min walking test;	
10.00 – Session ends.	10.31 – Session ends.	

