#### Physical activity

PA will be assessed using questionnaires and device-based measurements. The questionnaire from Jackson et al. [104] with a scale from 0 to 7 describing the overall PA level is complemented by questions about the amount of moderate-to-vigorous PA during a week. PA will also be measured with a tri-axial waist-worn accelerometer (X6-1a, Gulf Coast Data Concepts Inc., Waveland, MS, USA) with a dynamic range of ±6 g and a sampling frequency of 40 Hz. The accelerometer will be utilized during seven typical days at three time points: control, intervention and maintenance periods. A minimum of 3 days with 8 h of measurement will be accepted for analysis as it has been shown to provide adequate reliability for children and adolescents with CP GMFCS I [105]. Raw acceleration data will be transformed to Actigraph counts [106], in order to utilize validated GMFCS specific thresholds for different intensity zones for children with CP [107].

Specialized shorts with textile electrodes (Myontec Ltd., Kuopio, Finland, 108) will be utilized to record EMG bilaterally from quadriceps and hamstring muscles during an entire typical day. A small recording electronic module is able to collect muscle activity data for 8–12 h and can be analyzed offline afterwards. EMG signals will be acquired with a sampling frequency of 1 KHz and band-pass filtered (50–200 Hz, − 3 dB). The raw signals will be full wave rectified and averaged over 100 ms non-overlapping windows and stored into a portable module. Daily muscle inactivity, light, moderate and vigorous activity time of the participant will be extracted [108, 109]. Muscle inactivity will be defined as < 90% of the standing EMG activity for each muscle group. Moderate activity threshold is the preferred walking EMG activity, and vigorous activity is twice the amplitude of walking [110]. The participants will receive a diary to record times when the accelerometer and EMG pants are worn, facilitating the removal of non-wear time in the analysis.

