#### Biological maturity

To control for the confounding effect of maturation on the dependent variables during the study, estimated time from peak height velocity (i.e. maturity offset) will be computed using the sex-specific equation provided by Moore et al. [112]:
$$ \mathrm{Girl}'\mathrm{s}\ \mathrm{maturity}\ \mathrm{offset}=-7.709133+\left(0.0042232\ast \left(\mathrm{age}\ast \mathrm{height}\right)\right);{\mathrm{R}}^2=0.898;\mathrm{SEE}=0.528; $$$$ \mathrm{Boy}'\mathrm{s}\ \mathrm{maturity}\ \mathrm{offset}=-7.999994+\Big(0.0036124\ \mathrm{x}\ \left(\mathrm{age}\ \mathrm{x}\ \mathrm{height}\right),{\mathrm{R}}^2=0.896;\mathrm{SEE}=0.542. $$

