## Discussion

The current training intervention protocol combines different training modalities in an attempt to enhance motor function in people with CP. The individually tailored aspects are: 1) flexibility training for muscles diagnosed short in the Pre-tests; 2) the number of training sessions and strength exercises in each session will be adjusted depending, e.g., on the participants’ motivation, stamina and schedule; 3) introduction of a short isometric hold (3 s) in case that the joint range of motion is limited; 4) stabilization procedures to ensure proper execution of the movements, e.g., using a foam ball to prevent hip adduction during leg press.

The major limitation in this study is the effect of the growth spurt on the dependent variables. If it happens during the control period, results between pre-test 1 and 2 may be considerably different, making it harder for any intervention related changes to be statistically different. If the growth spurt happens during the intervention it may increase its effectiveness, whereas if it happens during the maintenance period it may slow down the adaptation loss. By carefully monitoring the maturity indicators it will be possible to understand and estimate how each participant was affected by the maturation process. A second limitation regards the study’s external validity: due to its length and great number of testing and training sessions, only participants and families that are already inclined towards higher levels of PA will likely choose to participate. Since PA levels are being measured objectively, it will be possible to characterize and compare this study with others and check this assumption.

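### The covariate rule lets intervention contrasts be adjusted for physical activity measured after training starts, on an undefined correlation trigger, and relies on a blunt growth control

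*Protocol article*

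**What the plan says.** Under Statistical analyses, change over time in the CP group is studied with a general linear mixed model over two pre-tests and one or two post-tests. The only sentence on confounders is that "variables such as PA levels or maturity offset will be controlled if they have a strong linear relationship with other dependent variables". It gives no threshold and does not say which PA measurement is meant.

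Three other sections bear on PA:
- Study purpose lists among the secondary hypotheses that "the EXECP intervention will: d) increase habitual PA".
- Physical activity sets the timing: "The accelerometer will be utilized during seven typical days at three time points: control, intervention and maintenance periods".
- Gait training makes walking at home part of the intervention. Participants are "asked to walk a minimum of 10 min per day every day for the duration of the intervention".

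On growth, Biological maturity says that "estimated time from peak height velocity (i.e. maturity offset) will be computed using the sex-specific equation", with the aim of controlling confounding by maturation. The Discussion names the growth spurt as the study's major limitation and adds: "By carefully monitoring the maturity indicators it will be possible to understand and estimate how each participant was affected by the maturation process". Height is measured in testing session 2 at both pre-tests and post-test 1. For the last visit, Testing sessions says: "The modified S2 performed in post-test 2 consists only of the gait tests and height measurement". Height is therefore scheduled at all four test points.

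**The concern.** PA after pre-test 2 is a consequence of treatment, if hypothesis (d) is right. It may also partly record the dose, because the daily home walking falls in the period when the accelerometer is worn. A model of walking distance, strength or gross motor function that includes concurrent PA no longer estimates the whole effect of the programme. It estimates the part that does not pass through activity.

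The trigger makes this worse. Adjustment is most likely for the outcomes that track PA closely, which are those with most to lose from it. With no stated threshold, the model for each outcome is chosen from that outcome's own data.

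The study has no randomised control group, so the intervention effect rests on within-person change. The handling of PA and growth therefore matters more than it would in a randomised comparison.

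**Working it through.** The plan gives no figure for this rule, so there is none to reproduce.

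**1. Effect lost by adjusting for concurrent PA.**
The Sample size section gives a smallest important change of 1.08, that is 8%, or ln 1.08 = 0.077 on the log scale. The share of the effect running through PA is not in the protocol. I assume 25-50%.
- 25% mediated: 8% × (1 − 0.25) = 6%.
- 50% mediated: 8% × (1 − 0.50) = 4%.

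A simulation shows the same in a random-intercept mixed model. It used 24 participants, three test points, a between-person SD of ln 1.46, a residual SD of ln 1.06 and 60 replicates per row. PA was assumed to rise by one between-person SD at post-test 1. The entries are the post-test 1 minus pre-test 2 contrast; the true value is 0.077.

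| Share through PA | No covariate | Concurrent PA | Maturity offset |
|---|---|---|---|
| 0% | 0.075 | 0.079 | 0.075 |
| 25% | 0.080 | 0.060 | 0.079 |
| 50% | 0.075 | 0.041 | 0.074 |
| 75% | 0.074 | 0.021 | 0.075 |

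Concurrent PA removes roughly the mediated share. Adjusting for the offset leaves the contrast where it was. No effect of growth on the outcome was built in, so the last column shows that the offset adds no bias. It does not show that the offset would correct for a spurt.

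**2. Precision of the trigger.**
With n = 24, the standard error of a correlation on Fisher's z scale is 1/√(24 − 3) = 0.218. A sample correlation of zero then has a 95% interval of about tanh(±1.96 × 0.218) = ±0.40. Sampling error alone can decide which outcomes pass an undefined threshold.

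**3. What the maturity offset registers in three months.**
The printed equations give a change of c × [(age + 0.25) × (height + growth) − age × height], with c = 0.0036124 for boys and 0.0042232 for girls. Ages, heights and growth are assumed.
- Man, 178 cm, no growth: 0.0036124 × 0.25 × 178 = +0.161 y.
- Boy aged 13, 155 cm, no growth: 0.0036124 × 0.25 × 155 = +0.140 y.
- Same boy, 2.5 cm growth: 0.0036124 × (13.25 × 157.5 − 13 × 155) = +0.260 y.
- Boy aged 9, 134 cm, 1.3 cm growth: 0.0036124 × (9.25 × 135.3 − 9 × 134) = +0.164 y.
- Woman, 165 cm, no growth: 0.0042232 × 0.25 × 165 = +0.174 y.
- Girl aged 11, 145 cm, 2.25 cm growth: 0.0042232 × (11.25 × 147.25 − 11 × 145) = +0.260 y.

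For the fast-growing boy, calendar age still supplies 0.140/0.260 = 54% of the change. In adults who have stopped growing it supplies all of it. The 9-year-old who is growing and the man who is not are almost indistinguishable (+0.164 against +0.161 y). In the simulated sample the three-month change averaged 0.19 y, against a between-person SD of about 3.4 y. The fitted coefficient would thus mainly reflect age differences between participants.

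**The case against.** The strongest reply is that the rule is conditional and silent on timing. Control-period PA would be harmless for a within-person contrast, and an unseen analysis plan may well specify it. PA also has other roles: it sets the number of weekly sessions, and it captures changes in outside activity, which the protocol allows to be reduced during training. In comparisons with the typically developing group, who attend only the pre-tests, PA is not a post-treatment variable at all. All of this stands. It limits the point to the intervention and retention contrasts, and makes the bias possible rather than certain. It does not remove the point, because the rule as written permits the harmful choice.

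On growth, a reader might infer that the offset is the wrong covariate, or that it cannot detect a spurt because its standard error of estimate (0.528-0.542 y, about 6.3-6.5 months) exceeds a three-month period. The documents do not support this. That error describes prediction across people, not within-person change, and the offset does respond to growth: 0.14 to 0.26 y in the example. Maturation is a legitimate confounder. The Discussion speaks of maturity indicators in the plural, and height is measured at every test point. The control period and the stated growth-spurt exception in Study purpose also mean that growth is not simply ignored.

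**Conclusion.** The point holds for PA. The rule allows the CP time contrasts to be adjusted for a variable that the intervention is meant to change, with no restriction to pre-intervention values and no defined trigger. The loss equals the share of the effect that runs through PA: an 8% gain would read as about 4-6% if that share were 25-50%. The share is assumed, and 8% is the protocol's smallest important change, not an expected gain. Harm requires the trigger to fire, concurrent PA to be used and mediation to be material. It should not be read as a claim that the published effect will be biased.

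The maturity offset is a lesser point. Over three months it mostly counts calendar age, so it would do little to correct for the confounder that the protocol calls its major limitation. It does not itself bias the contrast.

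**What to change.** Replace the covariate sentence in Statistical analyses with a rule that does four things:
1. For the intervention and retention contrasts in the CP group, do not adjust for PA measured after the intervention starts. Only control-period PA may enter. Concurrent PA belongs in a separate mediation analysis labelled exploratory.
2. Drop the correlation trigger and name one covariate set, fixed before analysis.
3. Use measured height as the time-varying growth covariate. Change since the previous visit is undefined at pre-test 1, so express it, for example, as change from pre-test 1 and set it to 0 at that visit.
4. Keep the maturity offset to describe the sample.

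This changes wording only. The height and PA measurements are already scheduled, and Study design defers data analysis until collection ends, flexibility tests excepted. The cost is one degree of freedom for the growth term.
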